**3.3 ENDPOINTS (PROTOCOLE REMINDER)**

**3.3.1 Primary endpoints**

G8 assessment will be performed using as a gold-standard tool the CGA questionnaires, tests, and scales: CIRS-G, ADL and IADL scales, Timed Get up and Go test, MNA, MMSE, and GS-15.

Especially, we will consider a patient as being at risk or requiring a complete CGA if we observe at least one of the following conditions:

CIRS-G: at least one grade ≥ 3 comorbidity (except for cancer),

ADL scale: a score below or equal to 5,

IADL scale: a score below or equal to 7,

Timed Get up and Go test: time strictly over to 20 seconds,

MNA: a score below or equal to 23.5,

MMSE: a score below or equal to 23,

GDS-15: a score over or equal to 6.

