Appendix S2 – ONCODAGE study protocol (abridged translation from French)

| **Study title** | Validation of a geriatric screening tool in oncology |
| --- | --- |
| **Acronym** | **ONCODAGE** |
| **Coordinating centre** | Institut Bergonié, Centre de Lutte Contre le Cancer, Bordeaux. |
| **Coordinator** | Pr. [name] |
| **Number of centres** | At least 15: the 15 Pilot Units of Coordination in Geriatric Oncology (*UPCOG*) along with health institutions members of the oncology network. |
| **Indication** | Patients over 70 years old with a cancer (colon, lung, ENT, breast, prostate, lymphoma), as part of the initial management. |
| **Trial rationale** | As patients age, risks for serious toxicity, or even lethality, during cancer treatment increase. A detailed assessment of the patient’s status is required.  Comprehensive geriatric assessment (CGA) is a method which has proved its usefulness but which is time-consuming and expensive to administer. A screening tool allowing the individualisation of patients who would benefit from a CGA is necessary.  In a previous regional prospective multicentre cohort (regional Ministry of Health-financed project, PHRC 2003), we studied patients over 70 years with cancers who were receiving first-line chemotherapy. This study enabled us to perform an exploratory study in order to develop a screening tool, the G8, which consists of a 7-item questionnaire from the Mini Nutritional Assessment (MNA) and an age indication. We applied the suggested screening tool to our population of 364 patients and this analysis provided encouraging results to be studied on a wider scale (Bellera et al., Ann Oncol, 2012). |
| **Expected effects** | With the use of this simple tool for screening, to be administered by nurses or oncologists, we consider that more elderly patients with cancer will be able to benefit from a CGA.  This tool will also enable us to rationalise the use of our geriatric assessment means and thus to focus their use on those who need it more, for more efficacy. |
| **Main objective** | Validate a new screening tool, the G8, to identify within a population of over 70-year-old patients with cancer those who need further geriatric assessment. |

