| **Hypotheses and statistical analyses** | **Hypotheses and required number of patients**  The objective is to maximise the sensitivity of the new screening tool and to obtain an estimation with a satisfying accuracy. Our exploratory study suggests (section 8) a sensitivity of about 90%, when we use as gold standard the presence of an abnormal score for at least one questionnaire, and a prevalence of 50% of patients with at least one abnormal questionnaire.  The inclusion of 1500 patients would help estimating the sensitivity on a 750-patient sample with abnormal CGA, with an accuracy of 2.4% for an expected sensitivity of 90% (*i.e.* 95% CI of 87.6% to 92.4%). In order to ensure a minimum of 1500 assessable patients, we will recruit **1650 patients**.  **Statistical analyses**  The population of the study will be described broadly according to its clinical and sociodemographic characteristics in terms of size and ratio for the qualitative variables and in terms of distribution for the quantitative ones.  The following parameters will be estimated:   - The sensitivity, the specificity, and the predictive values will be estimated. 95% CIs will be reported (binomial distribution). - The ROC curve representing graphically the sensitivity according to the (1 -specificity) for various thresholds of the assessed test will be represented graphically and help determine the area under the curve (AUC). - Internal consistency will be assessed according to Cronbach’s alpha coefficient. A 95% CI will be reported. - Reproducibility will be assessed by the intraclass correlation coefficient for quantitative variables. For qualitative variables, reproducibility will be assessed by Cohen’s kappa. - Scores between acknowledged subgroups will be compared thanks to a variance analysis. - Both G8 and VES-13 questionnaires will be compared thanks to their respective area under the curve. - We will assess whether using both screening tools together (G8 and VES-13) helps obtaining a more effective screening tool compared to the sole use of one questionnaire. |

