**Accuracy assessment:**

**The internal consistency** of each questionnaire will be assessed from answers to every item and according to Cronbach’s alpha coefficient,

The reproducibility will be assessed

- Inter-judges mistakes for G8: comparing the questionnaire filled by the oncologist and the same questions for G8 filled by the nurse (IGE) for each item and the overall score,

- Test-retest for VES-13: comparing the self-questionnaire filled by the patient during the oncology consultation to the questionnaire filled during the geriatrics consultation. This study will be conducted in three centres only: Bordeaux, Lille, and Lyons (60 patients per centre. See chapter 16.1.2 for a justification of the number of patients).

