**Assessment of the discriminating validity:**

A comparison of the score obtained to G8 and VES-13 between different groups according to the expected risk level of geriatric disorder will be performed to assess whether these questionnaires help discriminating populations for which we expect score differences (for instance, patients over 85 *vs.* patients under 85, palliative *vs.* non-palliative…).

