3.4.1.2 Estimation of the VES-13 reproducibility

The test-retest reproducibility study for the VES-13 questionnaire will be performed on a sample of patients from the Oncodage study. Pearson’s reproducibility coefficient after one month for the English VES-13 in a population of patients over 70 treated by anti-androgens for a prostatic cancer (Mohile et al., 2007) was 0.92 overall (respectively 0.52, 0.60, and 0.70 for the subsets concerning health perception, physical and functional disabilities) but data for the intraclass correlation coefficient were not found in the literature for the VES-13 test-retest assessment.

For two measures, the inclusion of 160 patients would provide an estimation for the intraclass correlation coefficient of 0.6 with an accuracy corresponding to a 95% CI of 0.2 width, *i.e.* 95% CI = [0,5-0,7] (Bonett, 2002).The accuracy obtained will be even better if the obtained coefficient is higher.

In order to be sure of getting 160 patients assessed by the VES-13 at both times (oncologic consultation and geriatric assessment), it has been decided to included 180 patients, corresponding to the first 60 patients who will be included in the three participating centres (Bordeaux, Lille, Lyons).

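### The G8 shares seven of its eight items with the MNA, itself one element of the reference standard, and no planned analysis shows how well the G8 detects non-nutritional abnormalities

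*Protocol*

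**What the plan says.** The synopsis (Trial rationale) describes "the G8, which consists of a 7-item questionnaire from the Mini Nutritional Assessment (MNA) and an age indication". Section 3.3.1, like the synopsis, sets the reference: "we will consider a patient as being at risk or requiring a complete CGA if we observe at least one of the following conditions". Seven conditions follow, on CIRS-G, ADL, IADL, Timed Get up and Go, MNA, MMSE and GDS-15. The MNA condition is "MNA: a score below or equal to 23.5", and it is sufficient alone.

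VES-13 is judged by the same criteria (section 3.3.2.1), and the synopsis adds: "Both G8 and VES-13 questionnaires will be compared thanks to their respective area under the curve". Section 3.4.1.2 describes the content of VES-13 when it reports earlier reproducibility coefficients: "respectively 0.52, 0.60, and 0.70 for the subsets concerning health perception, physical and functional disabilities".

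For discriminating validity, section 3.3.2.2 compares scores between groups expected to differ. It gives age as its first example ("for instance, patients over 85" against younger patients) and palliative status as its second.

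The CGA is done blind to both screening tools (section 3.3.1 and the synopsis). The only robustness analysis of the reference in section 3.4.3 varies the MMSE threshold. No analysis sets the MNA aside, and the overlap is not mentioned.

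**The concern.** When most of an index test is taken from a questionnaire that can by itself make the reference positive, part of their agreement reflects shared questions. The G8 is meant to decide who goes on to a full CGA, and section 3.3.1 puts the weight on avoiding false negatives. A high overall sensitivity could come largely from patients with nutritional problems, while patients whose only problem is cognition, mood, function or comorbidity are missed more often. The planned analyses would not show this.

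The consequences spread beyond the headline accuracy. The G8 threshold is chosen on this reference and then defines the groups in the survival analysis (section 3.4.3). The AUC comparison with VES-13 and the combined-tool analysis use the same reference. The planning value of 90% sensitivity was also obtained against a standard of any abnormal questionnaire (section 3.4.1.1).

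The age contrast has a similar weakness on a smaller scale. The G8 contains an age item, so some score difference between patients over and under 85 may arise whatever the other seven items show.

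**Working it through.** **The plan's own figure.** Section 3.4.1.1 takes 750 patients with an abnormal CGA and a prevalence of 50%: 750 / 0.50 = 1500 assessable patients, as stated. At a sensitivity of 0.90 the normal-approximation half-width is 1.96 × √(0.90 × 0.10 / 750) = 2.15 points. The exact binomial interval for 675/750 is 87.6% to 92.05%, so the stated 2.4% is its lower arm. The sample size is not in dispute here.

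**What an overall 90% can conceal.** Let w be the share of reference-positives with an abnormal MNA. Then

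overall Se = w × Se(MNA abnormal) + (1 − w) × Se(MNA normal, another element abnormal).

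The documents give overall Se = 0.90 as the expectation. They do not give w or the sensitivity among MNA-abnormal patients. Assuming 0.98 for the latter, Se(MNA normal) = (0.90 − 0.98w) / (1 − w):

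| w (assumed) | Se when MNA is normal |
|---|---|
| 30% | 0.87 |
| 50% | 0.82 |
| 70% | 0.71 |
| 80% | 0.58 |

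**Comparison with VES-13, MNA overlap only.** Simulation of 400,000 patients, all inputs assumed: two tools equally related to general frailty (loading 0.6), one of them also sharing MNA-specific variation (correlation 0.3 to 0.9), MNA abnormal in 20% to 40%, overall prevalence 50%. The MNA-sharing tool gains 0.03 to 0.21 in AUC against the full reference. Once the MNA is removed, the difference is zero to within 0.002.

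**Comparison with VES-13, both overlaps.** Now let the second tool share variation with ADL, IADL and Timed Get up and Go (assumed: seven domains, loadings 0.5 to 0.7, sharing 0.3 to 0.7, prevalence 50%). Against the full reference:

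- MNA abnormal in 30%: the MNA-sharing tool leads by about 0.02 to 0.07.
- MNA abnormal in 20%: the two are about level.
- MNA abnormal in 12% to 15%: the functional tool leads by about 0.01 to 0.04.

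Against the reference without the MNA, the functional tool leads by about 0.03 to 0.09 although it is no better. The sign of the tilt thus depends on a share that the documents do not give.

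**Age contrast.** Assume that the age item builds in a gap of 1 point, with SD 3 and groups of 150 and 1350. Then z = 1 / (3 × √(1/150 + 1/1350)) = 3.87, and power at the two-sided 5% level is Φ(3.87 − 1.96) = 0.97, with no contribution from the other items. The gap, SD and group sizes are not in the protocol.

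**Precision without the MNA.** If the MNA is the only abnormality in 30%, 50% or 70% of the 750 (assumed), 525, 375 or 225 positives remain. The half-width 1.96 × √(0.09/n) is then 2.6, 3.0 or 3.9 points.

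**The case against.** **Blinding and separate recording.** The oncologist records the G8, and a nurse fills in the MNA without sight of it. Section 3.3.2.2 treats the two sets of answers as separate ratings: "comparing the questionnaire filled by the oncologist and the same questions for G8 filled by the nurse (IGE) for each item". This stands: the G8 result itself is not used to build the reference, so this is not incorporation in the strict sense. But blinding guards against influence on the assessor. The same questions, put to the same patient, still enter both sides.

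**The target includes nutrition.** The protocol wants to detect any abnormal CGA element. Removing the MNA changes the target and counts correctly flagged MNA-only patients as false positives. This also stands. In an illustrative simulation (MNA abnormal in 30%, G8–MNA correlation 0.7 to 0.9), removal lowers the G8 AUC by 0.07 to 0.17 and sensitivity by about 2 to 4 points. Part of the AUC fall is the change of target and not bias. The MNA-free analysis is therefore a supplement and does not replace the primary one.

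**Other validity checks exist.** Section 3.3.2.4 uses the indication for geriatric intervention as an alternative reference, and section 3.3.2.2 uses mortality, progression and institutionalisation. These help only in part. The geriatrician who judges intervention works from an assessment that includes the MNA. The follow-up events share no items with the G8, but they address prognosis, not detection.

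**Scope.** Extra robustness tables are often left to an analysis plan, which is not shown here. That limits the weight of the point. Still, the protocol itself fixes the reference and names a robustness check for one element, and that element is not the one from which the G8 is drawn.

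**A stronger reading.** A reader might infer that the comparison with VES-13 is tilted towards the G8. The documents do not support that. VES-13 covers physical and functional disability, which ADL, IADL and Timed Get up and Go also measure.

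**Conclusion.** The point holds in limited form. The content overlap is a fact of the protocol, and as written the plan cannot separate detection of non-nutritional problems by the G8 from agreement with its parent questionnaire. The reported accuracy may be optimistic for those problems, but by how much cannot be derived. Every magnitude shown rests on assumed inputs, chiefly the share of positives due to the MNA.

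Three further conclusions would go too far. The validation is not circular as a whole, since the MNA is one of seven elements. An advantage for the G8 over VES-13 is not built in, because the net direction is open. And a rule that accepts G8 superiority only if it holds without the MNA would be one-sided: it removes the G8's overlap and leaves that of VES-13.

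The age point is minor. It concerns one example within a secondary endpoint, and the palliative contrast is unaffected. The protocol does not give the G8 scoring or say whether VES-13 scores age, so the 97% power figure only illustrates the mechanism.

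**What to change.** Keep the primary reference. In section 3.4.3, beside the MMSE robustness analysis, add:

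- (a) Sensitivity, specificity and AUC of both tools against the six-element reference without the MNA, with the share of reference-positives that are positive on the MNA only. State that MNA-only patients count as negatives here, so that specificity and AUC are read accordingly.
- (b) Sensitivity of both tools by individual CGA element, so that the MNA overlap of the G8 and the functional overlap of VES-13 are both visible.
- (c) A statement that the G8 versus VES-13 AUC comparison will be interpreted in the light of (a) and (b), with no superiority claim made to depend on the MNA-free reference alone.

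In section 3.3.2.2, use the G8 score without its age item for the over versus under 85 contrast, and treat VES-13 likewise if it scores age.

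No new data are needed, only a few tables. The costs are wider intervals in (a) and figures that may look less favourable to the G8.

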**These assessments will be performed blindly from the G8 and VES-13 answers.**

We will assess, for various thresholds of the assessed tool, the performances of the new screening tool compared to the reference one, thanks to the following parameters:

**The sensitivity (Se)**, defined by the proportion of patients registered as “requiring an CGA” with the screening tool, among patients having at least one abnormal CGA element;

**The specificity (Sp)**, defined by the proportion of patients registered as “not requiring a CGA” with the screening tool, among patients “having no abnormal CGA element”;

**Youden’s index (J)**, synthesizing the sensitivity and the specificity: J = Se + Sp – 1.

**The positive predictive value (PPV)**, defined by the proportion of patients “having at least one abnormal CGA element”, among patients registered as “requiring an CGA” with the screening tool.

**The negative predictive value (NPV)**, defined by the proportion of patients registered as “having no abnormal CGA element”, among patients “not requiring an CGA” with the screening tool;

**The positive diagnostic likelihood ratios (DLR+)**, defined by the ratio of positive tests in patients with the disease (true positive) out of positive tests in disease-free patients (FN of false positive).

**The negative diagnostic likelihood ratio (DLR-)**, defined by the ratio of negative tests in patients with the disease (false negative) out of negative tests in disease-free patients (true positive).

The area under the ROC curve will help determining the overall efficacy of the assessed test and determining the threshold value to increase simultaneously sensitivity and specificity of the new screening tool, or to maximise sensitivity while keeping a satisfying specificity. We will try to maximise sensitivity in order to decrease the G8 false negative rates, which would not thus benefit from the best management later.

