| **Assessment criteria** | **Principal assessment criteria**  G8 assessment will be performed using as a gold-standard tool the complete CGA based on the following tests, questionnaires, and scales: CIRS-G, ADL and IADL scales Timed Get up and Go test, MNA, MMS, and GDS-15.  Especially, we will consider a patient as being at risk or requiring a complete CGA if we observe at least one of the following conditions:   - CIRS-G: at least one grade ≥ 3 comorbidity (except treated cancer), - ADL scale: a score below or equal to 5, - IADL scale: a score below or equal to 7, - Timed Get up and Go test: time strictly over to 20 seconds, - MNA: a score below or equal to 23.5, - MMSE: a score below or equal to 23, - GDS-15: a score over or equal to 6.   We will assess, for various thresholds of the assessed tool, the performances of the new screening tool compared to the reference one, thanks to the following parameters:   - Sensitivity and specificity, - Youden’s index (J), - The predictive values (positive or negative), - The diagnostic likelihood ratios (positive or negative), - The area under the ROC curve.   **Secondary assessment criteria**   - The validation of the French version of the VES-13 screening tool will be based on the same validation criteria than for G8 tool. - The assessment of the intrinsic qualities of G8 and VES-13 tools will be based on the accuracy (internal consistency, reproducibility) and validation assessment. - The assessment of screening tools in various clinical situations will be based on the estimation of sensitivity, specificity, and of predictive values of each screening tool according to: - the type of cancer, - the therapeutic strategy (locoregional, and locoregional and adjuvant treatment), - the stage of the disease (local, metastasis). - We will evaluate the number of interventions according to the CGA (change of the initial treatment irrespective of its nature, interventions of other specialists in other fields). |

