**3.3.2 Secondary endpoints**

3.3.2.1 Validation of the French version of the VES-13 screening tool

We will use the same validation criteria than for the G8 tool (see previous section): sensitivity, specificity, Youden’s index, predictive values, diagnostic likelihood ratios.

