**3.4 STATISTICAL FACTORS**

**3.4.1 Hypotheses and required number of patients**

3.4.1.1 Main analysis

For a screening tool, sensitivity and specificity are assessed jointly, although we tend to favour sensitivity as it could be damageable not to detect patients requiring a CGA. The objective then is to maximise the sensitivity of the new screening tool.

Our exploratory study suggests (Chapter 9):

a sensitivity of about 90%, when we use as gold standard the presence of an abnormal score for at least one questionnaire,

a prevalence of 50% of patients with at least one abnormal questionnaire.

Supposing that the real sensitivity for our G8 screening tool is 90%, we estimate that the inclusion of 750 patients with at least one abnormal questionnaire would be enough to estimate the sensitivity with a sufficient accuracy (2.4%) and to obtain a 95% CI between 88% and 92%. Supposing that 50% of our population will have at least one abnormal questionnaire, **1500 assessable patients** will be needed.

A patient is said to be assessable if CGA and G8 data are complete. In our exploratory study, only 309 patients out of 364 had all the necessary questionnaires for CGA (85%). In order to ensure a minimum of 1500 assessable patients, we will recruit 1650 patients.

If we want to estimate sensitivity according to the type of cancer, we will obtain an accuracy of +/- 6% for a sample of 200 patients (95% CI: 84% to 96%), and of about 5% for a sample of 400 patients (95% CI: 86% to 94%).

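### The definition of the negative likelihood ratio contradicts itself, and both likelihood ratios are worded as ratios of tests rather than of within-group proportions (minor)

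*Protocol*

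**What the plan says.** The likelihood ratios belong to the principal criteria. The Assessment criteria row of the protocol summary lists "The diagnostic likelihood ratios (positive or negative" among the performance measures for G8, and section 3.3.2.1 carries the same set over to VES-13: "sensitivity, specificity, Youden’s index, predictive values, diagnostic likelihood ratios".

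They are defined only once, in the list of measures in section 3.3.1 (after the statement on blinded assessment):

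- DLR+ is "defined by the ratio of positive tests in patients with the disease (true positive"), taken "out of positive tests in disease-free patients (FN of false positive").
- DLR- is "defined by the ratio of negative tests in patients with the disease (false negative) out of negative tests in disease-free patients (true positive").

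In the same list, sensitivity, specificity and both predictive values are each defined as a proportion with a named denominator. For sensitivity, that denominator is given by "among patients having at least one abnormal CGA element".

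The lists of parameters to be estimated, in section 3.4.3 and in the Hypotheses and statistical analyses row of the summary, do not mention the likelihood ratios. Nothing there corrects the definitions.

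**The concern.** There are two separate defects.

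1. **Cell labels.** The words for the DLR- denominator describe true negatives, but the bracket names true positives, a cell from the other disease group. In DLR+ the words and the label false positive agree, and only the abbreviation FN is out of place.
2. **Form.** A likelihood ratio compares a proportion among patients with the condition with a proportion among those without it. As worded, each ratio sets tests against tests, with no division by the number of patients who have, or do not have, an abnormal CGA.

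Likelihood ratios are reported because they do not depend on prevalence. A ratio of counts loses that property. A DLR- that uses the bracketed cell no longer involves specificity. Section 3.3.1 puts the emphasis on avoiding false negatives, so DLR- is the ratio whose misstatement would matter more.

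**Working it through.** The protocol states no likelihood-ratio value, so there is no figure to reproduce. The check compares the definitions as written with the standard ones.

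**Inputs**

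- Sensitivity 90%. Section 3.4.1.1 expects "a sensitivity of about 90%, when we use as gold standard the presence of an abnormal score for at least one questionnaire".
- Prevalence of an abnormal CGA 50%, and 1500 assessable patients, hence 750 with and 750 without (section 3.4.1.1).
- Specificity has no planning value in the protocol. Assumed 40%, 60% and 80%.
- Prevalences of 60%, 70% and 80% are assumptions, used to show sensitivity to the planning value.

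**Standard forms**

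DLR+ = Se/(1-Sp) = [TP/(TP+FN)]/[FP/(FP+TN)]

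DLR- = (1-Se)/Sp = [FN/(TP+FN)]/[TN/(FP+TN)]

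At Se 90% and Sp 60%: DLR+ = 0.90/0.40 = 2.25 and DLR- = 0.10/0.60 = 0.167, at every prevalence.

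**Reading A: the DLR- bracket is followed**

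The ratio becomes FN/TP = (1-Se)/Se. With the planned figures, FN = 75 and TP = 675, so 75/675 = 0.111. Specificity does not enter:

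| Assumed Sp | Standard DLR- | FN/TP |
|---|---|---|
| 40% | 0.250 | 0.111 |
| 60% | 0.167 | 0.111 |
| 80% | 0.125 | 0.111 |

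The ratio of the bracketed value to the standard one is Sp/Se, for example 0.60/0.90 = 0.67. Whenever specificity is below sensitivity, a negative screen therefore looks more reassuring than it is. This holds at the planned 50% prevalence as well.

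The stray FN in the DLR+ bracket, if it were followed, would give TP/FN = 675/75 = 9.0. The same bracket also names the correct cell, so this is not a likely reading.

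**Reading B: the words are followed, as counts**

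With prevalence p,

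TP/FP = [p/(1-p)] × Se/(1-Sp) and FN/TN = [p/(1-p)] × (1-Se)/Sp.

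Both standard ratios are multiplied by the odds of an abnormal CGA. At N = 1500, Se 90% and assumed Sp 60%:

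| Prevalence | TP, FN, FP, TN | Factor | TP/FP (standard 2.25) | FN/TN (standard 0.167) |
|---|---|---|---|---|
| 50% (planned) | 675, 75, 300, 450 | 1 | 2.25 | 0.167 |
| 60% (assumed) | 810, 90, 240, 360 | 1.5 | 3.375 | 0.250 |
| 70% (assumed) | 945, 105, 180, 270 | 2.33 | 5.25 | 0.389 |
| 80% (assumed) | 1080, 120, 120, 180 | 4 | 9.0 | 0.667 |

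At the planned prevalence the two groups are equal in size and the count ratios are right. Above it, both are too large, and below it, both are too small.

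Readings A and B are alternatives: A follows the bracket and ignores the words, and B does the reverse. Their errors should not be added or quoted together as one result.

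**The case against.** The case for leaving this alone has several parts.

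- **The words outside the brackets name the right cells.** This stands for both ratios. A reader might infer that both likelihood ratios are defined with the wrong cells, but the text does not support that. The wrong-cell contradiction is clear only for DLR-, and in DLR+ the fault is one stray abbreviation.
- **The document calls itself an abridged translation from French.** This stands. The French text is not available, so the error cannot be placed in the original protocol. The English text is still the one that readers use.
- **The phrase about tests can be taken as loose wording for within-group rates**, since the measures carry their standard names and sensitivity and specificity are correctly defined beside them. This is a fair reading, and a statistician may well program the standard formula. It does not make the wording adequate, because the neighbouring measures are all given explicit denominators.
- **At the planned prevalence the count ratios are correct.** True for reading B, at 50% only, and section 3.4.1.1 treats that figure as a supposition. It does not rescue the bracketed DLR-.
- **Nothing else depends on these ratios.** This stands. A reader might infer that the primary validation is compromised, but the sample size rests on sensitivity, the threshold is chosen from the ROC curve with weight on sensitivity, and the two tools are compared by AUC. Anyone can recalculate both ratios from the reported sensitivity and specificity.

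**Conclusion.** The point holds as a minor correction. The DLR- definition contradicts itself, the DLR+ bracket contains a stray label, and both ratios lack the within-group denominators that make them likelihood ratios. Section 3.3.1 is the only place where they are defined, so the protocol contains nothing that settles the matter.

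The size depends on how the text is read. With the bracket, DLR- is 0.111 instead of 0.167 at the planned sensitivity and an assumed specificity of 60%. With the words taken as counts there is no error at 50% prevalence, and both ratios are 1.5 times too large at 60% and 4 times at 80%. Specificity and every prevalence other than 50% are assumptions. The documents do not show that wrong values were or will be computed, only that the definitions permit them.

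**What to change.** In section 3.3.1, replace the two definitions by

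- DLR+ = Se/(1-Sp) = [TP/(TP+FN)]/[FP/(FP+TN)]
- DLR- = (1-Se)/Sp = [FN/(TP+FN)]/[TN/(FP+TN)]

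and say that they apply to both G8 and VES-13. Disease status here means at least one abnormal CGA element. If the slips arose in translation, correcting the English text is enough. A confidence-interval method may be named for these ratios, but that is optional and is not part of this point.

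The cost is two lines of text. No data collection, sample size or other analysis changes.
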